### Sample size

Sample size calculation was based on the primary outcome (NTB total score). In the original FINGER trial [8], an effect size of 0.127 (Cohen’s d) was reported for the 2-year change from baseline on the NTB total score following a multidomain lifestyle intervention. In the LipiDiDiet trial [13], an effect size of 0.17 (Cohen’s d) was reported for the 2-year change from baseline on the NTB total score following an intervention with Souvenaid. As FINGER-NL combines a multidomain lifestyle intervention with Souvenaid, an effect size (Cohen’s d) of 0.20 (SD = 1) for NTB total score was anticipated for the 2-year change from baseline on the NTB total score in the HI-group compared to the LI-group. With a power of 90%, 2-sided significance level of α = 0.05 and an anticipated drop-out rate of 12.5%, a total of 1,206 subjects (603 per group after randomization) was considered adequate to detect the desired effect size.

### Statistical analyses

In alignment with other WW-FINGERS studies, we will test for change in the primary and secondary outcome variables, both within-group and between-group using linear mixed models with random effects for intercept (individuals) and slope (time). Time and randomization group will be entered as fixed effects, study site will be included as fixed covariate. Change in the outcome variables will be modelled by including the interaction term between randomization group and time as fixed effect. The intention-to-treat principle will be used. Missing primary and secondary outcome data will be handled through restricted maximum likelihood (REML) estimation of expected scores in the mixed models. Given the size of FINGER-NL, no additional covariates will be included in the primary model, and differences between individuals will be treated as random nuisance parameters in the REML model [48]. For the primary outcome, the level of significance will be set at 0.05 (two-sided). The Benjamini–Hochberg correction will be used to account for multiple comparisons of correlated secondary and exploratory outcomes.

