**Blood-based markers**				
Cholesterol (total, HDL, LDL + triglycerides)	x	x	x	Secondary
HbA1c	x	x	x	Secondary
Plasma glucose	x			Secondary
Creatinine	x			Secondary
APOE genotyping	x			Exploratory
Aβ 40/42, p-tau, NfL, GFAP, BDNF	x		x	Secondary

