**Questionnaires/other**				
A-IADL-Q^c^	x	x	x	Secondary
LIBRA	x	x	x	Secondary
EQ-5D-5L	x	x	x	Secondary
MCLHB-DRR	x		x	Exploratory
Metamemory in Adulthood Questionnaire	x	x	x	Secondary
Hill-Bone Medication Adherence Scale	x	x	x	Secondary
MIND-NL Eetscore FFQ^d^	x	x	x	Secondary
3-day food diary via Traqq app	x	x	x	Secondary
SQUASH	x	x	x	Secondary
LASA Sedentary Behavior Questionnaire	x	x	x	Secondary
Pittsburgh Fatigability Scale	x	x	x	Secondary
SARC-F Sarcopenia Questionnaire	x	x	x	Secondary
7 days Physical Activity Record^b^	x	x	x	Secondary
Insomnia Severity Index	x	x	x	Secondary
7 days Sleep diary	x	x	x	Secondary
Pittsburg Sleep Quality Index	x			Secondary
Five Facet Mindfulness Questionnaire	x	x	x	Secondary
Perceived Stress Scale	x	x	x	Secondary
Lubben Social Network Scale	x	x	x	Secondary
De Jong Gierveld Loneliness Scale	x	x	x	Secondary
9-item Patient Health Questionnaire (PHQ-9)	x	x	x	Secondary
Cognitive Reserve Index Questionnaire (CRIq)	x	x	x	Secondary

*Abbreviations*: *Aβ 40/42* amyloid-beta 40/42, *A-IADL-Q* Amsterdam Instrumental Activity of Daily Living Questionnaire, *APOE* Apolipoprotein E, *BDNF* brain derived neurotrophic factor, *EQ-5D-5L* 5-level EuroQol-5D, *FFQ* Food Frequency Questionnaire, *GFAP* glial fibrillary acidic protein, *HbA1c* hemoglobin A1c, *HDL* high-density lipoprotein, *LDL* low-density lipoprotein, *LIBRA* LIfestyle for BRAin health, *MCLHB-DRR* Motivation to Change Lifestyle and Health Behavior for Dementia Risk Reduction scale, *MIND* Mediterranean-DASH Intervention for Neurodegenerative Delay, *NfL* neurofilament light, *p-tau* phosphorylated tau, *SQUASH* Short QUestionnaire to ASsess Health-enhancing physical activity

^a^Including items on smoking and alcohol consumption

^b^Only measured among subgroup of participants (study site Groningen; *n* = 240)

^c^Completed by study partner

^d^Monthly assessment

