### Secondary outcomes

Secondary outcome measurements include 2-year change on the individual cognitive test performances (see above), instrumental activities of daily living (Amsterdam Instrumental Activity of Daily Living Questionnaire (A-IADL-Q) [33]), quality of life (5-level EuroQol-5D (EQ-5D-5L) [34]), modifiable dementia risk (‘LIfestyle for BRAin health’ (LIBRA) score [23, 24]), and several intervention-specific outcomes (physical activity (maximum grip strength, physical activity (SQUASH questionnaire [35]), sedentary behavior (LASA Sedentary Behavior Questionnaire [36]) and sarcopenia (SARC-F Sarcopenia Questionnaire [37])), fatigability (Pittsburgh Fatigability Scale [38]), 7 days Accelerometry (ActiGraph GT9X) combined with 7 days Physical Activity Record (Groningen study site only), cognitive training (cognitive function, meta-memory (Meta-memory in Adulthood Questionnaire [39])), cardiovascular risk factor management (blood pressure, cholesterol (total, HDL, LDL + triglycerides), blood glucose (HbA1c), waist circumference, BMI, medication adherence (Hill-Bone Medication Adherence Scale [40])), nutritional counselling (nutritional intake (Traqq app [41]), adherence to MIND-NL-Eetscore Food Frequency Questionnaire [42]), sleep counselling (sleep behavior (7-day sleep diary), insomnia (Insomnia Severity Index [43])), stress management (mindfulness (Five Facet Mindfulness Questionnaire [44]), perception of stress (Perceived Stress Scale [45])), and social activities (perceived social support (Lubben Social Network Scale [46]), emotional and social loneliness (De Jong Gierveld Loneliness Scale [47])). In addition, we will analyze blood-based biomarkers for Alzheimer’s disease (Aβ42/40, p-tau), axonal damage (NfL), astrocytes activity/injury or stress (GFAP) and brain plasticity (BDNF).

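### The random-slope model set for all secondary outcomes does not suit the five blood biomarkers, which are measured only at months 0 and 24

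*Protocol article*

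**What the plan says.** All places are in the protocol article.

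- **Model (Statistical analyses).** One specification covers the primary and all secondary outcomes: "we will test for change in the primary and secondary outcome variables, both within-group and between-group using linear mixed models with random effects". The random effects are an intercept per individual and a slope over time. On the fixed part: "Time and randomization group will be entered as fixed effects, study site will be included as fixed covariate". The treatment effect on change comes from "including the interaction term between randomization group and time as fixed effect". Estimation is by REML, which is also how missing outcome data are handled. No exception is made for outcomes with fewer visits. The section does not say whether intercept and slope are correlated, or whether time is the nominal visit or the actual date.
- **Schedule (Table 2, Blood-based markers).** The row "Aβ 40/42, p-tau, NfL, GFAP, BDNF" is marked at two of the three visits, months 0 and 24, and its type is Secondary.
- **Outcome list (Secondary outcomes).** The same markers are named for analysis: "In addition, we will analyze blood-based biomarkers for" Alzheimer's disease, followed by NfL, GFAP and BDNF.
- **Once-only variables (Table 2).** "Plasma glucose", creatinine and "Pittsburg Sleep Quality Index" are marked at month 0 only, also with type Secondary. The Secondary outcomes section, which is framed as 2-year change, lists none of the three. It names HbA1c for blood glucose, and the sleep diary and Insomnia Severity Index for sleep.

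**The concern.** A random intercept, a random slope and a residual error can be told apart only if each person has enough visits. A slope through two points fits each person exactly, so residual error cannot be separated from variation in slopes. The article applies the random-slope model without exception to outcomes that have just two points.

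At stake is whether the stated analysis of five secondary outcomes will run. If it is refused or does not converge, another specification is needed, and the article gives none.

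**Working it through.** **Inputs.** Biomarker visits are at 0 and 2 years (Table 2). Random intercept, random slope and residual are taken from Statistical analyses. N = 1,210 randomized (Results), and anticipated dropout is 12.5% (Sample size). The article gives no figure for this point that could be reproduced.

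**Step 1: count parameters against moments.** Let a be the intercept variance, b the intercept–slope covariance, s the slope variance and e the residual variance. With times 0 and 2:

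- Var(Y₀) = a + e
- Cov(Y₀, Y₂) = a + 2b
- Var(Y₂) = a + 4b + 4s + e

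That is three equations in four unknowns. The rank of the Jacobian of these moments gives:

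| Visits | Random effects | Moments | Parameters | Rank |
|---|---|---|---|---|
| 0, 24 months | correlated | 3 | 4 | 3 |
| 0, 24 months | uncorrelated (b = 0) | 3 | 3 | 3 |
| 0, 12, 24 months | correlated | 6 | 4 | 4 |

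In the uncorrelated case, s = (Var(Y₂) − Var(Y₀))/4. The model can then match the data only if the month-24 variance is at least the baseline variance.

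**Step 2: show the ridge.** Assume Var(Y₀) = 0.9, Cov = 0.7 and Var(Y₂) = 1.1. Then a = 0.9 − e, b = (0.7 − a)/2 and s = (1.1 − a − 4b − e)/4:

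| e | a | b | s |
|---|---|---|---|
| 0.10 | 0.80 | −0.05 | 0.10 |
| 0.15 | 0.75 | −0.025 | 0.075 |
| 0.20 | 0.70 | 0 | 0.05 |
| 0.25 | 0.65 | 0.025 | 0.025 |

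Check of the first row: 0.80 + 4(−0.05) + 4(0.10) + 0.10 = 1.1. Check of the last row: 0.65 + 0.10 + 0.10 + 0.25 = 1.1. All four sets are admissible and give the same covariance matrix.

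**Step 3: see what happens to the treatment effect.** One data set was simulated with N = 1,210, five sites and 12.5% missing at month 24. All four parameter sets gave the same REML log-likelihood (−779.6925), group-by-time estimate (0.1095) and standard error (0.0239). The uncorrelated model gave the same three values. The variance split is lost, but the tested effect is not.

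**Step 4: try actual visit dates.** With an assumed SD of 1 month around month 24, the log-likelihood over the same four sets ran from −780.86 to −779.85, a range of about 1. Identification is therefore weak. The estimate stayed at 0.110.

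**Step 5: count observations.** At 12.5% dropout there are 1,210 + 0.875 × 1,210 ≈ 2,269 observations for 2 × 1,210 = 2,420 random effects. With complete data the two counts are equal at 2,420. This is why software may refuse the model.

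**Step 6: gain from baseline adjustment.** Assume equal variance σ² at both visits and correlation ρ. Per person, a change score has variance 2σ²(1 − ρ), and the baseline-adjusted month-24 value has σ²(1 − ρ²). The ratio is (1 + ρ)/2, a reduction of (1 − ρ)/2: 10% at ρ = 0.8 and 5% at ρ = 0.9. The article gives no ρ for these markers.

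**The case against.** **The fourth parameter is not in the text.** The article names two random effects and no covariance between them. This stands: it would be too strong to say that the model cannot be identified under any reading. The other readings help little, because uncorrelated effects leave the model just identified, and only when variance does not fall over time, while actual dates leave it weakly identified.

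**The tested quantity is untouched.** This also stands. A reader might infer that the biomarker comparisons would be biased or invalid. The ridge calculation shows otherwise, since estimate and standard error do not change along it.

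**The simplest repair nearly works.** A reader might also infer that keeping only a random intercept would harm the analysis, because it forces equal variance at both visits. Random-intercept and unstructured 2×2 models were compared in simulated data (N = 1,210, five sites, 20 runs per setting, assumed ρ of 0.8 or 0.9, month-24 SD 1.0 or 1.2 times baseline). With complete data, estimate and standard error agreed. With 12.5% random dropout, the ratio of standard errors stayed between 0.990 and 1.004. Dropping the slope alone would therefore cure the fitting problem. It would still forgo the gain from baseline adjustment.

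**The detail may stand elsewhere.** A reader might infer that the covariance structure will be picked after the data are seen. The documents do not support that: no analysis plan is shown, and the Data Availability section says that analysis protocols can be requested. What remains is that the article itself fixes one model for all secondary outcomes and a visit schedule that does not suit it.

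**The once-only variables are a labelling matter.** The Secondary outcomes section never lists them, so no invalid test and no change in the multiplicity family can be shown.

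**Conclusion.** The point holds in a limited form. For the five biomarkers, the stated model in its usual form (correlated effects, nominal times) has four variance parameters for three moments and may not fit or converge. Its other readings are just identified or weakly identified. The group-by-time effect and its standard error stay identified, so no bias in any biomarker comparison follows. The primary outcome is measured at three visits and is not affected.

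The parameter count rests on the article alone. The ridge figures rest on assumed variances. The 5–10% variance reduction rests on assumed correlations and equal variances; it is a gain in efficiency from the proposed analysis and does not measure harm done by the non-identification.

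**What to change.** Add a sentence to the analysis specification for outcomes measured at two visits: drop the random slope and analyse the month-24 value adjusted for baseline. Either of these would serve:

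- ANCOVA with group, baseline value and site. This uses participants with a month-24 value.
- A two-visit model with a common baseline mean across groups, site, and an unstructured 2×2 covariance. This keeps the REML handling of missing data and also yields the within-group change that the article wants to report.

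In Table 2, align the type given for plasma glucose, creatinine and the Pittsburgh sleep index with the Secondary outcomes section, for example as baseline descriptors.

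The cost is one sentence and three table labels. It needs no new data, visits or participants, because the baseline biomarker values are already scheduled.

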### Randomization and blinding

Participants were randomized after providing written informed consent and after completing the baseline visit. Participants were allocated randomly into either the HI-group or the LI-group using a computer random number generator with randomly varied permuted blocks of 4 to 6 and an equal 1:1 allocation ratio, stratified by study site. Randomization took preferably place per 24 participants per site simultaneously, resulting in balanced HI-groups and LI-groups of 12 participants each and equal starting point of the intervention. To promote blinding and adherence, and inspired by U.S. POINTER [26], we deliberately avoid the label ‘control group’, but rather designate both groups as receiving some form of lifestyle intervention, differing however in structure and intensity. Personnel collecting the primary outcome measures (cognition) and researchers conducting the statistical analyses are blinded to group allocation.

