### Intervention program

#### High-intensity intervention

The HI-group follows a personalized, supervised and hybrid intervention, addressing a combination of 7 lifestyle components and 1 nutritional product. The 2-year intervention consist of 24 monthly online group meetings (duration: 90-min; 2–4 lifestyle domains addressed each meeting) and 8 three-monthly group meetings at the study site (duration: 120 min; 4–5 lifestyle domains addressed each meeting), all guided by a lifestyle coach, resulting in a total of 32 group meetings. The group meetings are supplemented with 6 individual sessions with a lifestyle coach to personalize the intervention (phone/video consultations; duration: 10–60 min; one or more specific lifestyle domains addressed each meeting depending on the needs and goals of the participant following the principles of motivational interviewing). Finally, participants have access to a digital intervention platform to engage in individual online sessions (duration: 5 min up to four hours per week) and access to additional, carefully selected or custom-made training material (e.g. videos, apps) throughout the intervention period. To avoid overload and foster adherence, lifestyle components are initiated in a stepwise manner and the burden of the intervention is deliberately distributed over 24 months. See Table 1 and Additional file 1 for an overview of all intervention domains and activities. Each group is guided through the intervention by a local intervention team, consisting of an experienced lifestyle coach and a study navigator. The (certified) lifestyle coach is responsible for the actual execution of all intervention modules and activities as well as personalizing the intervention. Professional profiles differed, but the majority of lifestyle coaches was physiotherapist or dietitian. The study navigator (no specific background; e.g., study nurse or junior researcher) is the site-specific primary contact point for participants and provides (ad-hoc) individual support and ongoing encouragement to achieve maximum adherence and reduce dropouts.

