A known challenge of longer-term trials is the adherence of participants to the intervention. Inspired by the original FINGER trial and U.S. POINTER [8, 26], participants in the high-intensity intervention arm have been placed in groups of approximately 12 individuals to encourage social/peer support among participants. Another challenge was the recruitment of a large number of study participants necessary for this trial. We primarily recruited via the Dutch Brain Research Registry, which is an online registry of individuals interested in participating in neuroscience studies [22]. It currently includes over 40.000 registrants, mainly middle‐to‐late age cognitively normal elderly. A dedicated recruitment campaign was launched for current and new registrants. The registry was then used to prescreen participants based on demographic, lifestyle and (other) risk factors for dementia and to invite people for further telephone screening performed by one of the five FINGER-NL study sites. We made the choice to pre-screen based on self-reported risk factors of cognitive decline. Whilst this may have been less precise, it was effective in keeping recruitment feasible. Based on the baseline characteristics, this strategy indeed resulted in a population with sufficient potential for prevention. The room for improvement in terms of lifestyle (mean LIBRA score) is slightly higher in the FINGER-NL sample compared with the original FINGER trial [21].

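### The primary model and the sample size leave out the coach-led groups of about 12 in the high-intensity arm, so both assume zero within-group correlation of change

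*Protocol article*

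**What the plan says.** **Delivery.** The Discussion states that "participants in the high-intensity intervention arm have been placed in groups of approximately 12 individuals to encourage social/peer support among participants". Under High-intensity intervention, the 24 online and 8 on-site meetings make 32 group meetings, and "Each group is guided through the intervention by a local intervention team, consisting of an experienced lifestyle coach and a study navigator". Randomization and blinding explains how the groups arise: participants were preferably randomised 24 at a time per site, "resulting in balanced HI-groups and LI-groups of 12 participants each", with a common start. The low-intensity arm gets 14 leaflets on the digital platform, and no group sessions are described for it.

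**Analysis.** The Statistical analyses section specifies "linear mixed models with random effects for intercept (individuals) and slope (time" as the random effects. Arm, time and their interaction are fixed effects, study site is a fixed covariate, and further covariates in the primary model are ruled out. Secondary outcomes use the same model.

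**Sample size.** An effect size "of 0.20 (SD = 1) for NTB total score was anticipated", with 90% power, two-sided 5% significance and "an anticipated drop-out rate of 12.5%, a total of 1,206 subjects (603 per group after randomization) was considered adequate". No ICC or design effect is mentioned.

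**The concern.** Randomisation was individual, but from then on high-intensity participants are treated together for two years, in groups meant to influence their members. Outcomes of people who share sessions, peers and a coaching team may be correlated. Low-intensity participants share no comparable setting. This is a partially nested design: one arm is clustered by delivery and the other is not.

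A model that knows only about individuals counts each high-intensity participant as a full independent piece of information. If changes are positively correlated within groups, the high-intensity mean change is less precise than the model reports. The confidence interval for the primary contrast is then too narrow, and the planned power is overstated. The fixed site effect does not repair this. It is a main effect, whereas the test is on change over time, and each site contains about ten high-intensity groups that can differ from one another. Between-arm tests of secondary outcomes inherit the problem.

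**Working it through.** **Inputs from the article.** d = 0.20, SD = 1, two-sided α = 0.05, power 90%, drop-out 12.5%, 603 per arm (Sample size); groups of about 12 (Randomization and blinding; Discussion); 1,210 randomised at five sites (Results).

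**Assumed.** The ICC of 2-year change within a high-intensity group, taken as 0.01, 0.02 and 0.05. SD = 1 is read as the SD of change (see step 5).

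**1. The plan's own figure.** The normal approximation gives 2(1.960 + 1.2816)²/0.20² = 525.4, so 526 per arm. The exact t-test needs 527. Allowing for drop-out, 527/0.875 = 602.3, so 603 per arm and 1,206 in total. This matches the article exactly and leaves no allowance for clustering.

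**2. Number and size of groups.** 605/12 ≈ 50 high-intensity groups, about 10 per site. After 12.5% drop-out, m = 12 × 0.875 = 10.5 completers per group and n = 603 × 0.875 = 527.6 per arm.

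**3. Effect of clustering in one arm.** The variance of the high-intensity mean is multiplied by 1 + (m − 1)ICC and that of the low-intensity mean is unchanged. The variance of the contrast is therefore multiplied by

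VIF = 1 + (m − 1) × ICC / 2.

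Without clustering, d/SE = 0.20 × √(527.6/2) = 3.248. Then:

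- power of a test with the correct SE = Φ(3.248/√VIF − 1.960)
- type I error of the unadjusted test = 2[1 − Φ(1.960/√VIF)]
- total N for 90% power, per arm before drop-out = (2 + (m − 1)ICC)(1.960 + 1.2816)²/0.20², divided by 0.875, then doubled

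| Assumed ICC | VIF | Type I error, unadjusted test | Power, correct SE | Total N for 90% power |
|---|---|---|---|---|
| 0 | 1.000 | 5.0% | 90.1% | 1,204 |
| 0.01 | 1.047 | 5.5% | 88.8% | 1,260 |
| 0.02 | 1.095 | 6.1% | 87.4% | 1,318 |
| 0.05 | 1.238 | 7.8% | 83.2% | 1,488 |

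The last column uses the normal approximation, hence 1,204 and not 1,206 in the first row. With m = 12 in place of 10.5, type I error at ICC 0.01, 0.02 and 0.05 is 5.6%, 6.3% and 8.3%, and power is 88.5%, 86.9% and 82.0%.

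**4. Check by simulation.** A t-test on change with 50 high-intensity groups of 12, independent low-intensity participants, 12.5% drop-out and 20,000 runs per setting rejected a true null in 5.1%, 5.9%, 5.8% and 8.2% of runs at ICC 0, 0.01, 0.02 and 0.05. All are within 0.4 percentage points of the formula.

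**5. Dependence on the meaning of SD = 1.** The composite is standardised on baseline SDs (Primary outcome), so SD = 1 could instead be the SD of the baseline score. With equal SDs at both visits and correlation r between them, the SD of change is then √(2(1 − r)). At r = 0.5 this is 1 and the table is unchanged. At r = 0.6 it is 0.894, and power is 94.4% at ICC 0.01 and 90.4% at ICC 0.05. The article gives no r. The type I error column does not depend on this reading.

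**The case against.** Several arguments on the other side have force.

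- **The type I error figures need a particular null.** Participants were randomised individually and the groups formed afterwards. If the intervention changes cognition for nobody, coaches and peers create no within-group correlation and the test keeps its 5%. The inflated figures require real group-specific effects that average zero. This stands, and it limits what the table shows.
- **Shared batch effects largely cancel.** Season and start date are common to the high-intensity and low-intensity halves of a batch, so they should not bias the standard error much. This also stands.
- **The ICC may be small.** Cognition is tested objectively by staff blinded to allocation. Much of the intervention is individual: six coach sessions, online sessions and the nutritional product. At ICC 0.01 the loss is little more than one point of power. This is fair, but it does not support assuming exactly zero when the groups were formed to produce peer influence.
- **The model follows related trials, and a fuller analysis plan may exist.** A sensitivity analysis for clustering may be specified elsewhere. The article does, however, fix the random effects, the covariates and the basis of the power calculation, and the point concerns those statements.

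A reader might go further and infer that the primary test is certainly anti-conservative, or that 90% power is simply wrong. The documents do not support this: they give no ICC, and the power loss depends on SD = 1 being the SD of change. A reader might also project much larger errors from a high ICC or from a few coaches each leading many groups. The article gives no number of coaches, and does not say whether one coach stays with a group throughout or leads several, so such figures would have no basis in it.

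**Conclusion.** The concern holds in conditional form. The article describes a partially nested trial but fixes a primary model and a sample size that contain no delivery-group or coach level. Both rest on an unstated assumption of zero within-group correlation of change in the high-intensity arm. If the assumption fails in the positive direction, the standard error of the primary contrast is too small.

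The likely size is modest: over assumed ICCs of 0.01 to 0.05, about one to seven points of power, and a type I error between 5.5% and 7.8%. The power figures assume SD = 1 for change and about 10.5 completers per group. The error figures assume zero average effect with genuine variation between groups. Because the anticipated effect is only 0.20 SD, even a modest understatement of the standard error could decide a borderline result. Intervention-specific secondary outcomes such as social support or physical activity may be more strongly correlated within groups than cognition, though the article gives no figures for these either.

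**What to change.** Before unblinding:

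1. Add to the primary model a random delivery-group-by-time effect with a separate variance in each arm. It belongs on change and not only on the intercept, because groups form after baseline. Code groups in both arms, using the high-intensity groups and the matching low-intensity batches of about 12, under masked arm labels. A term placed in the high-intensity arm alone would tell the analysts which arm is which, against the blinding described under Randomization and blinding; a symmetric specification avoids this.
2. Use Satterthwaite or Kenward-Roger degrees of freedom, and say in advance what is done if a group variance is estimated as zero.
3. Where a coach led more than one group, add a sensitivity analysis with coach as the cluster.
4. Apply the same structure to the between-arm secondary analyses.
5. State that the 90% power assumes no within-group correlation, say whether SD = 1 refers to change or to the baseline score, and report power over a small ICC range.

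**Cost.** One added random term and revised wording. Confidence intervals may be slightly wider and the stated power slightly lower. No new participants or data collection are needed, since group membership is part of how the intervention was delivered.
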